#### Module 6: effective problem-solving skill

In this module, participants will learn a problem-solving skill. A meta-analysis reported that problem-solving was effective in the treatment of depression in adults, with Cohen’s d = 0.83 (95% CI: 0.45 to 1.21) compared with control conditions [47]. Additionally, a previous Cochrane review reported that a problem-solving skill, often included in CBT interventions, was effective in the primary prevention of stress-related outcomes, including occupational stress and depressive symptoms, among healthcare workers [4]. Theoretically, a rational problem-solving skill must (1) clarify a problem to be addressed, (2) generate potential solutions to cope with the problem, (3) evaluate each solution, (4) implement selected solutions, and assess the result [48]. [name] will teach the nurse, [name], each step in the process. This module’s homework includes a problem-solving exercise involving stressful situations that participants encounter in their workplace or everyday life.

### Intervention group

Participants in the intervention group will be expected to complete one module a week. Each week, one module will be delivered, and all modules will be delivered in 6 weeks after the program starts. Every Monday, the research center will send a reminder email to those who have not completed each module.

### Control group

Participants in the control group will receive the iCBT program after the six-month follow-up. The participants in the intervention group and the control group will be able to undergo treatment as usual (TAU), such as stress management education or training provided by the nursing association. Few lectures address the knowledge and skills involved in CBT in such education or training. After the six-month follow-up, the iCBT program will be provided to participants in the control group for 9 weeks upon their request.

### Outcomes

Table 2 shows an assessment schedule of this study’s outcome measures. All primary and secondary outcomes except for the onset of MDE will be assessed at the baseline (T1), three-month follow-up (T2; immediately after the completion of the intervention), and six-month follow-up (T3). The onset of MDE will be assessed at the baseline and six-month follow-up. Only participants in the intervention group will be assessed regarding the usability of the iCBT program and their satisfaction with it at the three-month follow-up. Information contamination will be assessed at the three- and six-month follow-ups. All data will be collected using web-based self-report questionnaires. At the three- and six-month follow-ups, the research center will send at least two reminder emails to those who have not responded to the questionnaires.

**Table 2 Tab2:** Assessment schedule of the outcome measures for this study

Measurement	Aim	Baseline (T1)	3-M F/U (T2)	6-M F/U (T3)
Primary outcome				
BDI-II	Severity of depression	x	x	X
Secondary outcomes				
CIDI	The onset of MDE	x		x
JCQ	Psychosocial work environment	x	x	x
UWES	Work engagement	x	x	x
HPQ	Work performance	x	x	x
Sick leave days	Sick leave days during the past 3 months	x	x	x
Intention to leave	Intention to leave their organization	x	x	x
Knowledge and self-efficacy	Current knowledge of and self-efficacy in relation to the five components of the CBT program	x	x	x
Process evaluation				
Usability and satisfaction	Usability and satisfaction of the iCBT program		x	
Others				
Contamination	Contamination of information		x	x

Note: *BDI-II* Beck Depression Inventory II, *CIDI* WHO-Composite International Diagnostic Interview, *MDE* Major Depressive Episode, *JCQ* Job Content Questionnaire, *UWES* Utrecht Work Engagement Scale, *HPQ* WHO Health and Work Performance Questionnaire, *CBT* Cognitive Behavioral Therapy

### Primary outcome

#### Depressive symptoms

The Beck Depression Inventory-II (BDI-II) is a self-report inventory that evaluates depression severity. BDI-II includes 21 items measuring depressive symptoms, such as sadness, pessimism, suicidal thoughts or wishes, tiredness or fatigue, loss of energy, and loss of pleasure [49, 50]. Each item is scored on a four-point scale ranging from 0 to 3. Higher scores indicate higher depression severity. The Japanese version of the BDI-II developed by Kojima et al. (2002) has shown the same internal reliability and validity as the original version [51].

### Secondary outcomes

#### Incidence of MDE

The onset of MDE will be assessed using the online version of the Japanese WHO-CIDI v 3.0 depression section based on the DSM, Fourth Edition, Text Revision (DSM-IV-TR) criteria [23, 52]. CIDI is a structured diagnostic interview, administered by trained individuals to the general population [53]. The Japanese version of the WHO-CIDI v 3.0 was developed by Kawakami et al. (2005), and its validity in diagnosing MDE has been confirmed [23]. The online version asks respondents the same set of questions using the skip logic of the depression section. A computer program with an algorithm specific to WHO-CIDI v 3.0 automatically diagnoses MDE. The online version has been shown to be consistent in the clinical diagnosis of MDE, [54] and the reliability of this version has been confirmed in a 1-year test-retest survey [55]. While WHO-CIDI v 3.0 was originally designed to generate a diagnosis based on the DSM-IV-TR criteria, its instrument can also generate a diagnosis of MDE according to DSM-5 criteria [56].

#### Psychosocial work environment

Psychosocial work environment will be evaluated using the Japanese version of the Job Content Questionnaire (JCQ) [57, 58]. The JCQ is a 22-item self-administered instrument designed to measure the psychosocial environment in the workplace, based on Karasek’s Job Demands-Control model [59] and the Demand-Control-Support model [60]. The JCQ scales consist of psychological demands (5 items), job control (9 items), supervisor support (4 items), and coworker support (4 items). Each item is scored on a scale from 1 (*strongly disagree*) to 4 (*strongly agree*). The reliability and validity of the Japanese version of the JCQ are acceptable [57].

#### Work engagement

Work engagement is a new concept from a positive perspective of mental health. Work engagement will be measured using the short form of the Japanese version of the Utrecht Work Engagement Scale (UWES-J) [61, 62]. UWES-J consists of nine items measuring three subscales (i.e., vigor, dedication, absorption). Each item is assessed on a seven-point scale from 0 (*never*) to 6 (*always*). The total score is calculated from all nine items. The reliability and validity of the UWES-J have been established [62].

#### Work performance

Work performance will be evaluated using one item of the WHO Health and Work Performance Questionnaire (HPQ) [63]. The HPQ is a self-report measure designed to estimate the workplace costs of health problems. In this study, participants will be asked to rate their overall work performance during the past 4 weeks. Items are scored on an 11-point scale ranging from 0 (*worst possible performance*) to 10 (*best possible performance*). A high score indicates a high degree of work performance.

#### Sick leave days during the past three months

Participants will be asked to report their number of sick leave days during the past 3 months.

#### Intention to leave

Intention to leave will be measured using the Japanese version of the four-item scale used by Geurts, Schaufeli, and De Jonge [64, 65]. The scale is a self-report inventory assessing the extent to which respondents expressed an intention to leave their organization during the last month. Each item is scored on a scale from 1 (*strongly disagree*) to 5 (*strongly agree*). Higher scores indicate greater intention to leave. Reliability and validity of the Japanese version have not yet been determined.

#### Knowledge and self-efficacy

Participants will be asked to rate their current knowledge of and self-efficacy in the five CBT components of the program (stress management, behavioral activation, cognitive reconstruction, relaxation training, and problem solving). The items assessing knowledge will start with the question, “How much knowledge do you have about…” while the items assessing self-efficacy will start with “How confident are you that you can do…” Each item will be scored on a 5-point scale ranging from 0 (*none*) to 4 (*enough*). Higher scores indicate greater knowledge of and self-efficacy in CBT components.

### Psychological distress

Psychological distress will be measured only at baseline using the Japanese version of the K6 [30, 31]. Participants will be stratified at baseline based on K6 score (5 or greater or less than 5). The K6 is a self-report inventory assessing the frequency with which respondents have experienced symptoms of psychological distress during the past 30 days. Each item is scored on a scale from 0 (never) to 4 (all of the time). Higher scores indicate more severe psychological distress [66]. The internal reliability and validity of the Japanese version of the K6 are acceptable [30].

### Process evaluation

#### Usability of and satisfaction with the iCBT program

The usability of and satisfaction with the iCBT program will be assessed using original questions. Sample questions include, “How easy was it to understand the program?” and “How satisfied were you with the program as a whole?” Each item will be scored on a 5-point scale ranging from 0 (*none*) to 4 (*enough*). In addition, participants will be asked which device they used most frequently.

#### The number and types of modules and homework

The number and types of modules and homework will be evaluated using the e-learning system records.

### Contamination of information

Contamination of information will be assessed at three- and six-month follow-ups through one original question answered on a dichotomous yes/no scale: “During the past three months, have you received information on stress management from your colleagues who used this study’s iCBT program?”

### Demographic characteristics

Demographic data, including age, gender, marital status, education, employment status, position, years of experience as a nurse, and overtime hours during the past month will be collected.

### Sample size calculation

This study’s iCBT program will include mental health professionals’ support. Previous meta-analyses of iCBT aimed at improving depressive symptoms among workers, both with or without supports, yielded effect sizes of 0.16–0.25 [19, 20]. Programs with supports have been reported to be more effective compared to self-guided iCBT programs [15, 20]. To detect a small effect size of 0.2 or greater at an alpha error probability of 0.05 and a power (1-β) of 0.80 using G*Power V.3.1.9.2 [67], a sample size of 394 participants per arm would be required. Anticipating a dropout rate of 25%, the necessary sample size would be 525 participants per arm.

### Randomization

After the baseline survey, eligible participants will be randomly assigned either to the intervention or control group using stratified permuted-block randomization, with a random block size of two. Participants will be stratified based on K6 score (5 or greater or less than 5) at baseline survey and worksite. The intervention effect may differ according to the severity of the psychological distress at baseline. The K6 cut-off score will be based on the optimal cut-off value (i.e., 4/5), which was used to separate patients with mood disorders in a previous study [66]. An independent biostatistics researcher will generate a stratified permuted-block random table. This table will be password-protected and concealed to other researchers. The researcher (KK) will carry out enrollment and another independent researcher will conduct allocation. During the random assignment, only the researcher will be able to access the stratified permuted-block random table.

### Statistical methods

#### Clinical efficacy

For primary and secondary outcomes, except the onset of MDE, a mixed model for repeated measures conditional growth model analysis will be conducted on an intention-to-treat basis. We will analyze a group (intervention and control) * time (baseline and three- and six-month follow-ups) interaction as an indicator of intervention effect. Missing values will be imputed by applying maximum likelihood estimation using the MIXED procedure. As the surveys will be conducted via the Internet, missing values will not occur unless the participants do not answer the questions. Cohen’s d between groups and 95% confidence intervals will be calculated at each assessment term to assess effect size. The values of 0.2, 0.5, and 0.8 are generally interpreted as small, medium, and large effects, respectively [68]. In addition, we will also calculate the Number Needed to Treat (NNT) because of the difficulty of interpreting the effect size from a clinical perspective. The NNT is the number of persons who must be treated to yield a difference in the onset of an event in one person compared to the control group. In this study, the NNT to alleviate depressive symptoms to achieve improvement in one individual from subthreshold depression will be calculated. Based on the cut-off BDI-II score, this improvement was defined as a change from a score of 14 or more to a score of 13 or less.

Regarding the onset of MDE, a survival analysis will be performed to compare the intervention and the control groups in terms of their mean survival time without MDE to evaluate the effectiveness of the intervention. The survival time will be calculated for each participant as months from the baseline survey to the onset of MDE or the end of six-month follow-up survey. The cumulative incidence ratio of MDE and event-free survival ratio at the six-month follow-up will be estimated using the Kaplan-Meier method. To test the difference in survival probability between the intervention and the control group, a log-rank test will be performed.

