**Methods:**

Nurses working at three university hospitals, one public hospital, and twelve private hospitals who meet inclusion criteria will be recruited and randomized either to the intervention group or the control group (planned *N* = 525 for each group). The newly developed iCBT program for nurses consists of six modules, which cover different components of cognitive behavioral therapy (CBT); transactional stress model (in module 1), self-monitoring skills (in module 2), behavioral activation skills (in module 3), cognitive restructuring skills (in modules 4 and 5), relaxation skills (in module 5), and problem-solving skills (in module 6). Participants in the intervention group will be asked to read these modules within 9 weeks. The primary outcome will be depressive symptoms as assessed by the Beck Depression Inventory-II (BDI-II) at baseline, three-, and six-month follow-ups.

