### Objectives and hypotheses

This study has two purposes: (1) to develop a new six-week iCBT program for nurses in Japan and (2) to examine the effectiveness of this iCBT program in improving depressive symptoms as the primary outcome and prevention of the onset of major depressive disorder and improvement in psychosocial work environment, work engagement, and work performance as the secondary outcomes at three- and six-month follow-ups among nurses in Japan.

We hypothesize that the iCBT program will: (1) be associated with lower depressive symptoms at three- and six-month follow-ups among nurses; (2) reduce the risk of major depressive episode (MDE) at the six-month follow-up, and (3) improve the psychosocial work environment, work engagement, and work performance at three- and six-month follow-ups.

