## Methods

### Trial design

This study will be a two-arm parallel-group non-blinded RCT with three- and six-month follow-ups. Participants will be requested to complete a baseline online questionnaire. Subsequently, participants meeting the inclusion criteria will be randomly allocated either to the intervention or the control group at a 1:1 ratio. This study’s iCBT program will be provided to the participants in the intervention group for 9 weeks. All surveys will be conducted using online questionnaires. Online follow-up surveys will be implemented at three (immediately after the intervention) and 6 months after the baseline survey. After the six-month follow-up, the iCBT program will be provided to participants in the control group. The study protocol was registered at the University Hospital Medical Information Network (UMIN) Clinical Trials Registry (UMIN-CTR, ID = UMIN000033521). This manuscript was written according to the Standard Protocol Items: Recommendations for Interventional Trials (SPIRIT) guidelines [22].

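### The primary hypothesis covers two follow-up visits, but the deciding test is an interaction that cannot confirm both, and the sample size is one comparison tied to no visit

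*Protocol article*

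**What the plan says.** Four parts of the protocol article bear on the primary question.

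- **Outcome (Abstract, Methods).** "The primary outcome will be depressive symptoms as assessed by the Beck Depression Inventory-II (BDI-II) at baseline, three-, and six-month follow-ups". No visit is singled out as primary.
- **Hypothesis (Objectives and hypotheses).** The program will "be associated with lower depressive symptoms at three- and six-month follow-ups among nurses". Both follow-ups are named with equal standing.
- **Test (Statistical methods, Clinical efficacy).** "a mixed model for repeated measures conditional growth model analysis will be conducted on an intention-to-treat basis", and then: "We will analyze a group (intervention and control) * time (baseline and three- and six-month follow-ups) interaction as an indicator of intervention effect". No contrast, degrees of freedom or deciding visit is given. Cohen's d with a 95% confidence interval is to be reported at each assessment, as a measure of effect size.
- **Size (Sample size calculation).** "To detect a small effect size of 0.2 or greater at an alpha error probability of 0.05 and a power (1-β) of 0.80", "a sample size of 394 participants per arm would be required"; then "Anticipating a dropout rate of 25%, the necessary sample size would be 525 participants per arm". The section mentions no visit, SD scale, repeated-measures structure or correlation. Allocation is 1:1 (Trial design).

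**The concern.** Hypothesis, test and sample size each describe a different quantity. The hypothesis needs a benefit at two named visits. The interaction asks only whether the arms' profiles over three visits differ somewhere, with no direction and no visit. The sample size is for one difference at an unspecified time.

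The model name adds a second ambiguity. A repeated-measures model with time as visits gives a 2-df interaction, whereas a growth model with a linear trend gives a 1-df difference in slopes. These behave very differently if the benefit fades after the intervention ends. A significant interaction could be reported as support for a two-visit hypothesis when the benefit has gone by six months, or a real three-month benefit could be missed, depending on which model is fitted.

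**Working it through.** **Inputs from the article:** d = 0.2, alpha 0.05, power 0.80, 394 per arm before dropout, 25% dropout, 525 per arm, 1:1 allocation, visits at baseline, three and six months.

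**Assumed, because the article does not give them:** the correlations and the SD scale of d (ranges shown), compound symmetry with within-person correlation ρ, and 394 per arm with data at the visits.

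**1. Reproduce the plan's figure.** Normal approximation, two-sided: n = 2(1.960 + 0.842)²/0.2² ≈ 392.4, so 393. The two-sample t-test gives 394 (power 0.8006; 393 gives 0.7996). One-sided would give 310. Dropout: 394/0.75 = 525.3. The stated numbers are therefore correct for one two-sided comparison of two means.

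**2. The interaction as a 2-df test.** Let δ = (δ3, δ6) be the between-arm differences in change from baseline, in raw-score SD units. The covariance of the two changes is (1−ρ)[[2,1],[1,2]], so the noncentrality is

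λ = (n/2) × 2(δ3² − δ3δ6 + δ6²) / [3(1−ρ)].

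- Lasting effect (0.2, 0.2): the bracket is 0.04 − 0.04 + 0.04 = 0.04.
- Effect gone by six months (0.2, 0): the bracket is 0.04 − 0 + 0 = 0.04.

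The two patterns give the same λ at every ρ. With n/2 = 197, λ = 5.253/(1−ρ); at ρ = 0.5, λ = 10.51. Against the 5% critical value for 2 df:

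| ρ | Rejects for (0.2, 0.2) | Rejects for (0.2, 0) |
|---|---|---|
| 0.3 | 69% | 69% |
| 0.5 | 83.5% | 83.5% |
| 0.7 | 97% | 97% |

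**3. The interaction as a linear slope.** With equally spaced visits and compound symmetry, the slope contrast reduces to the baseline-to-six-month change. Power = Φ(δ6 √197 / √[2(1−ρ)] − 1.96). At ρ = 0.5:

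- (0.2, 0.2): Φ(2.807 − 1.96) = 80.2%.
- (0.2, 0): Φ(−1.96) = 2.5% in the favourable direction, at any ρ.

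For a three-month-only benefit at ρ = 0.5, the two model names thus give 83.5% or 2.5%.

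**4. Requiring both visits at 0.05 each** (no alpha adjustment needed).

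- If 0.2 is standardised on the tested contrast, each visit has about 80% power. Joint power is 64% when the two test statistics are uncorrelated (0.80² ≈ 0.64), 69% at correlation 0.5, 71.5% at 0.7 and 75% at 0.9. Reaching 80% would take 490 per arm at 0.5 (654 after dropout) or 471 at 0.7 (628).
- If 0.2 is in raw-score SD units and change from baseline is tested, joint power is 51%, 69%, 80% and 91.5% at ρ = 0.3, 0.5, 0.6 and 0.7.
- With baseline adjustment it is 72% at ρ = 0.3 and 82% at 0.5, crossing 80% at about ρ = 0.47.

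**5. Either visit at 0.05** (a rule the article does not state). Familywise error is 1 − 0.95² = 9.75% if independent, 9.1% at correlation 0.5 and 7.0% at 0.9.

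**The case against.** The strongest reply has three parts.

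First, this is a condensed article. Contrasts, degrees of freedom and testing order are commonly left to an analysis plan, and 394 and 525 are arithmetically sound. That is fair as far as missing detail goes. But the article states a hypothesis, a deciding quantity and a size, and these three do not match. That is a mismatch in what is written.

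Second, a reader might infer that every possible reading forfeits 5% error, 80% power or the ability to answer the hypothesis, or that the stated power applies to no multi-visit reading. The documents do not support that. The 2-df interaction holds 5% error and has 83.5% power at ρ = 0.5 for a lasting effect. A both-visits rule holds 5% error, answers the hypothesis directly, and reaches 80% power at about ρ = 0.6 on change scores, or lower with baseline adjustment, if 0.2 is in raw-score units. A closed procedure (interaction first, then each visit at 0.05) also controls error. The article gives neither the SD scale nor the correlation, so a loss of power is possible but not shown.

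Third, a reader might infer that the plan inflates error by letting whichever visit is favourable decide. It states no such rule: the interaction is the indicator, and the per-visit Cohen's d is for effect size. The 7.0–9.75% figure describes only what would follow if that rule were used.

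What remains is that the article names none of the protective rules, and the test it does name cannot separate a lasting benefit from a vanished one.

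**Conclusion.** The point holds in this form: the stated test does not answer the stated two-visit hypothesis, and the stated power is demonstrated only for a single comparison at an unnamed visit.

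The identical rejection rates for lasting and vanished benefit are exact under compound symmetry; another covariance structure would change the figures. The slope result rests on the same assumption with equally spaced visits. Whether 80% power survives a both-visits rule depends on two inputs the article does not give: 64–75% if 0.2 is on the tested contrast's scale, and 80% or more from moderate within-person correlation if it is in raw-score units. The sample size arithmetic itself is not in question.

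**What to change.** Treat time as categorical visits. Replace the omnibus interaction as the decision test with named between-arm BDI-II contrasts from the mixed model, under one success rule, and keep the omnibus as descriptive.

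One suitable rule is to test the three-month difference at two-sided 0.05, then the six-month difference at 0.05 only if the first is significant. Three months is defensible because the Background describes the meta-analytic effects (g = 0.25 and 0.15) as post-intervention, the sample size section cites the same sources, and the Trial design section places the three-month survey directly after the intervention. The sample size section should then say that 394/525 and the 80% refer to that first contrast.

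Requiring both visits is an equally legitimate choice and closer to the hypothesis as written. It needs no alpha adjustment, but the sample size section should then state the SD scale and correlation behind d = 0.2 and restate the joint power, re-sizing if it falls short.

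Cost: wording in the protocol and any analysis plan or registry entry, with no additional data. Under the fixed sequence no extra participants are needed, but the six-month claim becomes conditional on the three-month result. Under the both-visits rule the recruitment target may rise.

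### The planned group-by-time test estimates change from baseline, while 394 per arm matches an unadjusted comparison of scores; adjusting for baseline BDI-II is more precise at no cost

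*Protocol article*

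**What the plan says.** In the protocol article, Statistical methods (Clinical efficacy), all primary and secondary outcomes except onset of a major depressive episode go into a mixed model, named both as a repeated-measures model and as a conditional growth model. The treatment effect is read from the group by "time (baseline and three- and six-month follow-ups) interaction as an indicator of intervention effect". Baseline is therefore a response level. The section names no baseline covariate and does not constrain the arms to a common baseline mean. It also promises a between-arm Cohen's d at every assessment.

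The Sample size calculation says "To detect a small effect size of 0.2 or greater at an alpha error probability of 0.05 and a power (1-β) of 0.80", and concludes that "a sample size of 394 participants per arm would be required". The 0.2 is chosen against earlier meta-analyses that "yielded effect sizes of 0.16–0.25". With 25% dropout the target becomes 525 per arm. The section gives no correlation between visits, does not say whether 0.2 is in SD units of follow-up scores or of change scores, and does not state whether the test is one- or two-sided.

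Table 2 shows that BDI-II is collected at baseline, three months and six months.

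**The concern.** With a free mean for each arm at baseline, a group-by-time contrast is the difference between arms in mean change from baseline. In a randomised trial the arms have the same expected baseline mean, so estimating two separate ones spends information on a difference known to be zero in expectation. A change score subtracts the whole of any chance baseline difference. The efficient analysis subtracts only the fraction rho of it (with equal SDs).

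The sample size, by contrast, was worked out as if scores were compared between arms with no use of baseline. The sizing and the test therefore rest on different variances, and the link between them is a correlation that the document does not give. The target effect is small, so the precision of the primary contrast matters.

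**Working it through.** **Inputs from the document.** alpha 0.05, power 0.80, d = 0.2, 394 evaluable per arm, 25% dropout, 525 randomised per arm, 1:1 allocation.

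**Assumptions.** Two-sided test (see step 1). 0.2 is in follow-up SD units (inferred, not stated). SDs are equal at baseline and follow-up. rho is taken from 0.3 to 0.8. Dropout is unrelated to outcome, and the effect is tested at a single follow-up visit.

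**1. Reproduce the stated figure.** A two-sided, two-sample t-test at d = 0.2 has power 0.7996 with 393 per arm and 0.8006 with 394, so 394 is exact. A one-sided test would need 310 (normal approximation). 394 / 0.75 = 525.3, in line with the stated 525. No correlation or repeated-measures term is needed to reach these numbers.

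**2. Variance per arm, in units of the squared SD.**

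- Unadjusted follow-up score: 1/394.
- Planned change contrast, complete cases: 2(1 − rho)/394.
- Planned change contrast, all 525 baselines in the likelihood: (1 − rho²)/394 + (1 − rho)²/525.
- Baseline-adjusted: (1 − rho²)/394.

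The last two differ by (1 − rho)²/525, which is positive for every rho below 1. That term is the price of leaving the baseline means free.

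**3. Power** = Φ(0.2/√(2v) − 1.96), where v is the variance per arm. Example at rho = 0.3:

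- Planned: v = 0.91/394 + 0.49/525 = 0.002310 + 0.000933 = 0.003243. √(2v) = 0.0805, 0.2/0.0805 = 2.48, power 70.0%.
- Adjusted: v = 0.002310. √(2v) = 0.0680, 0.2/0.0680 = 2.94, power 83.7%.

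| rho | Planned, complete cases | Planned, 525 baselines | Baseline-adjusted | Gain over 525-baseline column (points) |
|---|---|---|---|---|
| 0.3 | 66.0% | 70.0% | 83.7% | 13.7 |
| 0.4 | 72.7% | 75.9% | 86.5% | 10.6 |
| 0.5 | 80.2% | 82.6% | 90.0% | 7.4 |
| 0.6 | 88.1% | 89.6% | 93.9% | 4.3 |
| 0.7 | 95.2% | 95.9% | 97.6% | 1.7 |
| 0.8 | 99.3% | 99.4% | 99.7% | 0.3 |

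**4. Where the planned test equals the stated power.** Complete cases: 2(1 − rho) = 1, so rho = 0.50. With 525 baselines, set (1 − rho²)/394 + (1 − rho)²/525 = 1/394. Then (1 − rho)/rho = √(525/394) = 1.154, so rho = 1/2.154 = 0.46.

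**5. Does the pattern depend on testing one visit?** For a joint 2-df interaction test with d = 0.2 at both follow-ups, compound symmetry and 394 complete per arm, power at rho 0.3, 0.5 and 0.7 is 68.8%, 83.5% and 97.1% as planned, against 92.9%, 95.4% and 99.1% adjusted. The ordering is the same.

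**The case against.** The planned interaction test is unbiased in a randomised trial and keeps its type I error. A change contrast already takes baseline into account, and randomisation is stratified on K6. The article may also leave covariates to an analysis plan that is not shown. Validity is not in dispute. The K6 stratum is a two-level split of a different scale and controls BDI-II imbalance only in part. The article itself fixes baseline as a level of time in the effect test, so that choice can be commented on as it stands.

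The stronger objection concerns power. A reader might infer that the trial is underpowered, or that adjustment is needed to restore the stated 80%. The document does not support that inference:

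- It gives no rho, and nothing in it favours 0.3 over 0.7. At 0.7 the planned test already has about 96%.
- The analysis is by maximum likelihood on an intention-to-treat basis, so all 525 baselines count. This lifts the planned power above the complete-case figures.
- The scale of 0.2 is not stated. The exact t-test match and the promised between-arm Cohen's d at each assessment make follow-up SD units plausible, but do not establish them. If 0.2 was meant in change-score SD units, the planned test has the stated 80%.
- The model's name leaves open whether time is categorical or linear, so single-visit figures illustrate the power of the final test and do not settle it. With a linear slope and free baseline means, the test is still a contrast of changes.

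All four points stand. They limit any claim of a shortfall. They do not touch the efficiency comparison, which holds at every rho below 1.

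**Conclusion.** The point holds as an efficiency recommendation. The planned test estimates a difference in change, the 394 per arm was derived for an unadjusted comparison of scores, and a baseline-adjusted analysis is more precise at any rho below 1. Under the assumptions listed, the gain runs from about 14 percentage points at rho 0.3 to 7 at 0.5, 2 at 0.7 and 0.3 at 0.8.

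A shortfall from 80% is conditional. It needs 0.2 to be in follow-up SD units and rho to be below about 0.46 with all baselines in the likelihood, or 0.50 with complete cases. Neither condition can be confirmed from the document. The adjusted single-visit contrast does not fall below the stated power at any rho in the range, so the sponsor can benefit without knowing rho. This is a free improvement and not an error that threatens the trial.

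**What to change.** In Statistical methods (Clinical efficacy), replace the interaction with free baseline means by one of two near-equivalent models:

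- three- and six-month BDI-II as responses, with baseline BDI-II and its interaction with visit as covariates; or
- baseline kept as a response, with the two arms constrained to a common baseline mean. This retains everyone who has a baseline score and stays closest to the present wording.

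Do the same for the other continuous outcomes analysed with this model. Table 2 shows a baseline measurement for each.

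In Sample size calculation, state that 394 per arm is for an unadjusted comparison at a single visit, say which SD the 0.2 refers to, and note that the figure is conservative for the adjusted model if that SD is of follow-up scores.

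The cost is wording only. No extra participants, visits or measurements are needed. The change should be fixed before follow-up data are examined by arm.
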